#### Training

##### Usability and clarity

Adolescent participants respond to questions about ease of use (that is, “this module was easy to use”), ease of understanding (that is, “this module was easy to understand”), and ease of reading (that is, “this module was easy to read”) of the online intervention. Items are scored using a five-point Likert scale (1 = *strongly disagree* to 5 = *strongly agree*) [91]*.* In our pilot study, the Cronbach alpha for these scales were .94, .96 and .97, respectively [5,33].

##### Sociocultural relevance

Adolescents respond to statements about identification and relevance of the lesson. A sample item is “the module struck a chord with my own life.” Items are scored using a five-point Likert scale (1 = *strongly disagree* to 5 = *strongly agree*). In our pilot study, the Cronbach alpha was .96 [5,33].

##### Perceived benefits of cognitive behavioral principles

Perceived benefits of the cognitive behavioral principles taught in the intervention are measured by five questions, which are rated by adolescents on a ten-point Likert scale (1 = *very unhelpful* to 10 = *very helpful*), with higher scores indicating a stronger perceived benefit for learning cognitive behavioral therapeutic techniques [92]. A sample item is, “change my behaviors in ways that have improved my mood.” In our pilot study, Cronbach alpha was .92 [5,33].

##### Perceived benefits of interpersonal principles

Perceived benefits of the interpersonal principles taught in the intervention are measured by four questions (for example, “express my feelings and reactions to important people in my life”), to which adolescents respond on a ten-point Likert scale (1 = *very unhelpful* to 10 = *very helpful*), with higher scores indicating a stronger perceived benefit for learning interpersonal therapeutic techniques [92]. In our pilot study, the Cronbach alpha was .85 [5,33].

##### General information sheet

Participants provide demographic information about themselves at baseline and follow-up assessment points. Information collected includes age, date of birth, sex, height, weight, address, phone number(s), email address(s), race/ethnicity, school grades completed, parental marital status, family composition, and number of lifetime moves derived from the Four-Factor Hollingshead measure of social status.

##### Teen Behavior Questionnaire

The Teen Behavior Questionnaire (TBS) is a self-report questionnaire regarding diet, exercise, religion, and internet use. Questions vary in format, such as open ended, yes/no, and contain Likert scales of frequency (for example, “never” to “multiple times per day”).

##### Social Adjustment Scale

The Social Adjustment Scale (SAS-SR) is a self-report measure containing 36 items. The measure is designed to evaluate behaviors at school, with peers, and at home over the past 2 weeks (for example, “How many days of classes did you miss in the last 2 weeks?”) using a five-point ordinal scale (for example, “No days missed” to “I did not go to classes at all”).

##### Beck Hopelessness Scale

The Beck Hopelessness Scale (BHS) is a 20-item, true-false measure of the extent to which individuals are pessimistic about their future. The BHS has been shown to predict dropout from psychosocial treatment and poorer treatment response. The BHS has strong psychometric properties in adolescent samples; Cronbach’s alpha is .93 [93].

#### Safety

##### Suicide ideation scale

This is a scale used to assess the adolescent’s current level of suicidal tendencies. This measure is only used in response to adolescent reports of suicidal thinking. An example of a question asked is: If you were to weigh your reasons for living against dying, how would they compare? 0: Living outweighing dying; 1: about equal; and 2: for dying outweighing living [94].

##### Suicide intent scale

This measure is used when an adolescent has made a suicide attempt. It yields information about the seriousness of the attempt. An example of as question asked is: Did you make it hard for people to find you and to help you? 0: No precautions; 1: Passive precautions (for example, avoiding others but doing nothing to prevent their intervention); and 2: Active precautions, such as locking doors [95].

##### Lethality scale

This is a measure of the lethality of past suicide attempts, as reported by the adolescent. This does not have questions, but rather examples on a numerical scale based on intent scale. For example: 2.0: Death is improbable as an outcome of the act; if it occurs it is probably due to unforeseen secondary effects. Frequently the act is done in a public setting or is reported by the person or by others. While medical aid may be warranted, it is not required for survival. Or 10.0: Death is almost a certainty, regardless of the circumstances or interventions by an outside agent [96].

#### Adherence and log files

##### Time

Our time measures will be total time on the website in minutes, total time spent on story components in minutes, and duration of website use in days. To calculate the total time on the website in minutes, we will collect the time stamps of the first and last page loaded for each session (that is, each time a participant loads a module) and subtract the starting from the final time stamp. To avoid measuring time spent on other open pages, the length of time for each session will be capped at 7 minutes, the estimated amount of time required to review the material with a fifth grade reading level. The lengths of all sessions will be combined to create a variable for total time spent on the website measured in minutes. To calculate the time spent on the story component of the intervention in minutes, we will use a similar algorithm that subtracts the timestamp from when the story component is opened from the timestamp of when the following page is loaded. To calculate the duration of website use (the total number of days a participant spends on the intervention), we will count the number of days from the first login until the last day of the participant’s activity on the website.

##### Modules

For every participant, we will record the total number of modules completed. A module is considered complete if at least one exercise in that module is completed and/or the short online survey offered at the end of the module is completed.

##### Sessions

We define a session as the discrete occasion when a participant logs onto the website. Total number of sessions for each participant will be manually calculated by adding the total number of sessions per participant (if there was no activity after logging in, a participant is logged out after 7 minutes, but it still will be counted as a session).

##### Exercises

Exercise measures (percentage of exercises completed and number of characters typed) are used to measure the active behavior of participants. For each participant, we will calculate the percentage of exercises completed by adding the number of exercises completed across all modules and dividing this by the total number of available exercises. To measure the degree to which each exercise is completed, we will count the total number of characters typed by each participant across all modules.

### Statistical analysis

#### Survival analyses

Preceding the main analysis of whether the rate of MDD onset varies by intervention condition, we will test for constant hazard over time. If this test is not significant at 0.10 will use Cox proportional hazards, adjusted for age and sex, to compute the hazard ratio for adolescent major depressive episodes for the intervention group in comparison to the HE group. We will also test whether time to MDD depends on the interaction of intervention condition by baseline level of symptoms. If the test or diagnostics reveal nonproportional hazards (that is, there is evidence of differential effect over time), we will include this nonproportionality in analyses. We have used such limited “model fitting” tests without regard to the magnitude of intervention effect in previous analyses that still preserve the Type I error rate [97], and will follow multiple comparison procedures we have used previously to identify time intervals where significant effects are found [88].

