### Sample size

Our intent is to recruit and randomize 400 participants (200 per site). We anticipate being able to retain 80% of these youth throughout the two-years of follow-up. In [name]’s pilot study of the CATCH-IT intervention, of the 84 randomized participants, only 7 did not take part in any follow-up (91% retention) [5]. We implemented standard measures to minimize attrition: all adolescents who express challenges related to study participation are contacted by research staff; attempts are made to resolve their concerns so they can continue to participate; and standard methods are used to optimize retention (for example, birthday cards and regular updates on contacts). In keeping with an intent-to-treat design, all randomized cases who provide consent are followed and included in data analyses.

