#### Longitudinal data analysis

We test the hypothesis that the intervention affects the course of depressive symptoms and other measures across time. Our general method will be to use growth curve modeling with continuous outcomes to examine how the intervention changes adolescent depressive symptoms, vulnerability factors, educational impairment, and quality of life. Simple comparisons will be calculated as appropriate (for example, number of depressed days [98]), and survival curve modeling will be used for binary outcomes for prevalence of disorders [44,99-103]. Guided by our methods development on growth models, we will address missing data using full information maximum likelihood and multiple imputation, which provide improvement over “last observation carried forward” and other less refined methods [104-106]. We will also examine whether or not there are variations in growth trajectories by introducing covariate interactions and mixtures to growth models, techniques that we and our colleagues have developed [97,107-110]. These more complex models can characterize quantitatively differential response, as well as qualitative changes, such as recurrence [111]. All such models will be preceded by careful model checking [67,93,107,112].

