#### Sample size analysis

We conducted a series of power/sample size calculations through a SAS macro [124] under realistic alternatives to address impact on depressive symptoms. We require 200 adolescent subjects per intervention condition to achieve 80% power based on a conservative application of our pilot study findings from the CATCH-IT trial [33]. These calculations assume that in the control group, 72% are free from depression after one year follow-up, and the second year continues to follow the same exponential rate for controls; for intervention, the hazard is a constant ratio of 0.62, and an attrition rate of 7% for each of the first four quarters and 2% for each of the second four quarters. Note that the estimated hazard rate of 0.62 is two-thirds of that we observed in this previous study. There are concerns raised about the use of pilot study data to assess power, even using a lower value than we observed [125], so we conducted other power calculations based on the data from a similar study [45]. In their study, they found a departure from exponential and disproportional hazards of intervention over time. Assuming the same attrition rate as we found above, a study with 400 subjects would produce 80% power when the effect of CATCH-IT was only 60% at every interval of time relative to the CBT hazard rate in the Clarke study. Thus, we expect to have sufficient power even if the overall benefit is 60% of what was obtained by Clarke.

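### The main Cox model adjusts only for age and sex and omits baseline depression-risk measures the trial has, leaving the hazard ratio exposed if loss to follow-up tracks that risk differently by arm

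*Protocol article*

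**What the plan says.** Under Survival analyses, the main comparison of MDD onset is fixed as follows, provided a preliminary test on the hazards is not significant: the investigators "will use Cox proportional hazards, adjusted for age and sex, to compute the hazard ratio for adolescent major depressive episodes". A separate test of intervention by baseline symptom level is also planned. The section does not say how participants lost to follow-up are handled.

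Under Randomization, allocation is stratified by risk severity (CES-D score and prior major depression or dysthymia), age and site. The risk-severity factors are not among the stated Cox covariates.

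Under Beck Hopelessness Scale: "The BHS has been shown to predict dropout from psychosocial treatment and poorer treatment response".

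Under Longitudinal data analysis: "we will address missing data using full information maximum likelihood and multiple imputation". The same sentence says this is guided by the investigators' work on growth models.

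Two figures for loss are given. Sample size: "We anticipate being able to retain 80% of these youth throughout the two-years of follow-up". Sample size analysis: "an attrition rate of 7% for each of the first four quarters and 2% for each of the second four quarters".

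**The concern.** A Cox model that censors participants when they are lost gives a valid hazard ratio only if, among those with the same covariates, the lost have the same onset hazard as those who stay. Here the covariates are arm, age and sex. By stratifying on CES-D score and prior episodes, the protocol itself treats these as risk factors for onset. If adolescents at higher baseline risk also leave more often, and more so in one arm, that arm's risk set becomes progressively healthier and the hazard ratio moves without any treatment effect.

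The arms differ in contact. CATCH-IT adds provider interviews, coaching calls and check-in calls, whereas Health Education has routine provider contact. Different patterns of loss are therefore possible. At stake is the hazard ratio for the main endpoint, and the data needed to guard it are largely already collected.

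**Working it through.** **Expected loss.** From Sample size analysis: 1 − 0.93⁴ × 0.98⁴ = 1 − 0.7481 × 0.9224 = 0.310. From Sample size: 1 − 0.80 = 0.20. The 31% is gross. With onset competing, about 25% of controls and 27% of CATCH-IT participants would be censored by drop-out before an event.

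**The plan's own power figure.** The inputs are "in the control group, 72% are free from depression after one year follow-up", "for intervention, the hazard is a constant ratio of 0.62" and "We require 200 adolescent subjects per intervention condition to achieve 80% power". A two-sided 5% level is assumed, since none is stated.
- Control hazard: −ln 0.72 = 0.3285 per year. CATCH-IT: 0.3285 × 0.62 = 0.2037.
- Probability of observed onset over eight quarters with the stated attrition: 0.3901 and 0.2689.
- Events: 200 × (0.3901 + 0.2689) = 131.8.
- Schoenfeld: z = (√131.8 / 2) × |ln 0.62| − 1.96 = 5.740 × 0.4780 − 1.96 = 0.784, so power is 78.4%. It is 79.4% if losses fall at quarter end.

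This is close to the stated 80%, so the event and attrition inputs are read as intended.

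**Null simulations.** These assumptions are not in the document: a standard normal baseline risk score multiplies the onset and drop-out hazards per SD; the measured score has reliability about 0.9; 31% are lost in each arm unless stated; follow-up is cut back to the last of months 2, 6, 12, 18 and 24; N = 400; no true effect. Age and sex are left out because they are unrelated to risk in this set-up. Ranges cover separate runs of at least 2,000 trials per scenario; where no rate is given, none is quoted.

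| Onset multiplier | Drop-out multiplier, CATCH-IT / HE | HR, score omitted | Type I error | HR, score added | Type I error |
|---|---|---|---|---|---|
| 1.5 | 1.5 / none | 0.96–0.97 | 5.2–6.0% | 1.00 | 5.1% |
| 2.0 | 2.0 / none | 0.90–0.91 | 8.5–9.1% | 0.98–0.99 | 4.4–4.9% |
| 1.5 | 2.0 / 1.5 | 0.97 | 5.4% | – | – |
| 2.0 | 2.0 / 1.5 | 0.965 | 5.6% | – | – |
| 2.0 | none / 2.0 | 1.11 | – | – | – |
| any tried | same in both | 0.99–1.00 | – | – | – |

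The Monte Carlo standard error at 2,000 trials is √(0.05 × 0.95 / 2,000) = 0.5 percentage points, so the first row is hardly distinguishable from 5%. At 20% loss, the second row's type I error falls to 6.2%.

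**With a true hazard ratio of 0.62** (single fits, n = 40,000; onset multiplier 1.3 to 2.0). When the drop-out association differs by arm, the observed hazard ratio is 0.91 to 1.09 times its full-follow-up value. When the association is alike, the ratio is 0.97 to 1.00. Adding the risk score to the model returns 0.59 to 0.64, which is 0.62 within simulation error.

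**Gain without informative loss.** At a hazard ratio of 0.62, adding a score that carries 1.5 to 2.0 times the onset hazard per SD raises power by about 3 to 7 percentage points. Part of this is a change of estimand: with full follow-up and a multiplier of 2.0, the model without the score estimates 0.64 to 0.66 where the conditional value is 0.62.

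**The case against.** The strongest reply is that nothing in the document shows informative loss.

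- The hopelessness sentence concerns drop-out from psychosocial treatment. Under Sample size, every consenting randomized participant is followed and analysed, so stopping the programme is not censoring. Nor is treatment response the same as onset of MDD. A reader might infer that the protocol itself says loss to follow-up depends on depression risk. It does not, and the sentence is indirect support only. **This stands.**
- No arm difference is documented, and its direction is open. A reader might infer that loss would flatter CATCH-IT. The extra contacts are motivational and could equally retain adolescents at high risk, and dependence in Health Education only gives 1.11, against the programme. **This stands.**
- The 31% is one of two figures; the other is 20%. Also, K-LIFE covers the whole interval since the previous assessment, so a missed visit followed by a return need not censor. **This stands** and makes the effect smaller.
- Censoring weights, drop-out tables and sensitivity analyses are commonly left to the analysis plan, which is not shown. Their absence here is no defect. **This stands.**
- The missing-data sentence comes right after one that mentions survival modelling for binary outcomes, so it is arguable whether those methods cover the main endpoint. The text does not tie them to the Cox model, but it does not exclude it either. **This stands in part.**
- Baseline symptoms do enter a separate interaction test, and stratification balances risk at entry. **This does not answer the point.** Balance at baseline does not keep risk sets comparable after unequal loss, and the interaction test is not the main estimate.

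What remains is the covariate set, which the article does state.

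**Conclusion.** The point holds as a cheap improvement to a stated choice; it is not a demonstrated error. Adjusting for age and sex alone leaves the main hazard ratio dependent on an independent-censoring assumption that baseline risk measures could make weaker.

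Under one-arm dependence of 1.5 to 2.0 per SD and 31% loss, the null hazard ratio is about 0.97 to 0.91 and the type I error about 5% to 9%, with the mirror image if the dependence lies in the other arm. When both arms share some dependence, the type I error stays close to 5% (5.4% and 5.6% in the cases tabulated), and with equal dependence the bias is negligible. All of these strengths are assumptions.

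A reader could obtain a type I error of 13% to 16% by assuming a drop-out multiplier of 3.0 with an onset multiplier of 2.0, in CATCH-IT only and none in Health Education. Nothing in the document supports so extreme a case. Confidence that bias would occur in practice is low. The case for the change does not depend on it, because adjusting for prognostic and stratification factors is sound even if drop-out is harmless.

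**What to change.** In Survival analyses, extend the stated covariates of the main Cox model from age and sex to age, sex, baseline CES-D score and prior depressive episode. Add the Beck Hopelessness Scale score if it is measured at baseline; the article does not say when it is given. State which CES-D form is used, since both the ten-item and the 20-item versions appear. State one expected loss figure, or explain why 20% and 31% differ.

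Inverse-probability-of-censoring weights are an optional sensitivity analysis and may already be in the analysis plan.

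The cost is a change of wording and a little programming, with no new data if the scores are held at baseline. The hazard ratio becomes conditional on the added covariates and will usually lie somewhat further from 1 than the less adjusted one, so the report should say which is primary. Adjustment does not remove bias from loss driven by symptoms that arise after baseline.

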## Methods/Design

### Study design

This study is a 5-year, two-site randomized clinical trial to test the efficacy the CATCH-IT preventive intervention against the Health Education (HE) control program in preventing the onset of depressive episodes in an intermediate to high risk, geographically representative sample of adolescents aged 13 to 18.

We identify high risk adolescents based on elevated depressed mood scores (cut-off set to maximize sensitivity and specificity for future episodes; [14,50,51]). Enrolled adolescents are randomized into either the CATCH-IT or the HE group, and are assessed at baseline and at 2, 6, 12, 18 and 24 months post-intake on measures of depressive symptoms, depressive diagnoses, other mental disorders, and on measures of role impairment in education, quality of life, attainment of educational milestones, and family functioning in order to examine predictors of intervention response. Ethical bodies that approved this study are discussed in the Acknowledgements section.

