### Primary care site recruitment and implementation process

The primary care aspects of the study (including recruitment, provider motivational interview, and referrals to treatment, when clinically indicated) are centered in pediatric clinics in urban and suburban areas in both Chicago, IL and Boston, MA. Practices are recruited either by study staff or by health care providers at existing study sites. Healthcare providers (physicians and nurse practitioners) and office nursing staff (for example, registered nurses and medical assistants) are informed about the study and provide written consent to participate in specific roles described below. Each participating healthcare provider also completes pre- and postquestionnaires regarding the intervention, status of the clinic, and their experiences in participation. At each site, a research coordinator or study champion is identified to communicate with study staff about room scheduling, weekly recruitment times, positive and negative screens, and other study details. Providers and other medical professionals are instructed in the screening protocol. Office nursing staff conduct the screenings of the adolescents with the two question screening tool. Health care providers are trained in Motivational Interviewing either with a one hour program using a lecture/discussion format and example video tapes, a three-session training, or through more informal interactions with the study staff, using detailed scripts. Providers receive semi-structured feedback on their motivational interview technique after completing 1 to 2 interviews with teen participants at their clinic. Each motivational interview takes approximately 10 minutes to complete. Three interviews are completed over the course of the year with each participant, with each provider interviewing one to eight patients. Study-employed mental health professionals, who conduct three motivational phone calls with the participants during the intervention, are also trained in Motivational Interviewing. Throughout the study, study staff members are in frequent contact with the primary care clinics, discussing logistical details, reporting when screened adolescents require referral to treatment, and providing feedback about the clinic’s participation.

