### Randomization

Participants are assigned randomly to CATCH-IT or HE. Randomization was determined by a computer generated sequence and was blocked by practice and time of entry, and stratified by level of risk severity (based on CES-D score, prior episodes of either major depression or dysthymia), age (13 to 14 or 15 to 18) site (Chicago or Boston) [56,57].

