### The CATCH-IT intervention

The CATCH-IT intervention has an Internet component (with separate adolescent (14 modules) and parent (4 modules) programs) and a motivational component (three primary care physician motivational interviews at time 0, 2 months and 12 months, and one to three study-staff coaching phone calls either at 1 month (Chicago) or at 2 and 4 weeks and 18 months (Boston)). In addition to the motivational interviews and coaching phone calls, three “check-in” calls during weeks 1 to 3 are offered to participants; these calls are intended to ensure participants have access to the Internet and take approximately five minutes to complete.

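### The main Cox model adjusts for age and sex but leaves out risk severity and site, which stratify randomisation: the test stays valid but gives up some power

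*Protocol article*

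**What the plan says.** Under Survival analyses, provided a preliminary hazard test is not significant at 0.10, the article will "use Cox proportional hazards, adjusted for age and sex, to compute the hazard ratio for adolescent major depressive episodes" in CATCH-IT relative to the Health Education control. No other covariate set is given for the main analysis.

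Under Randomization, assignment "was blocked by practice and time of entry" and is "stratified by level of risk severity (based on CES-D score, prior episodes of either major depression or dysthymia"), together with "age (13 to 14 or 15 to 18) site (Chicago or Boston").

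Under Study design, high-risk adolescents are identified by elevated depressed-mood scores, with the "cut-off set to maximize sensitivity and specificity for future episodes".

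The omitted factors appear in the analysis plan only in other roles. Baseline symptom level is in a separate treatment-by-baseline interaction test (Survival analyses). Site and level of risk are among the moderators and subgroups (Moderator analysis). Neither severity nor site is entered as a main effect in the main model.

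**The concern.** The usual rule is that factors used to stratify randomisation are carried into the main analysis. Here age is kept, sex is added although it does not stratify, and risk severity and site are dropped without a stated reason. This is not a detail left to a later document, because the article names the covariate set.

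Two consequences follow if the omitted factors predict onset. Stratification balances the arms on them, and a model that ignores this overstates the standard error of the treatment effect. And because the Cox hazard ratio is non-collapsible, a model without prognostic factors estimates a ratio closer to 1 than the one conditional on them. Both weaken the test relative to an adjusted analysis. The design has little spare power, so a loss of several points would matter.

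**Working it through.** **Step 1: reproduce the stated power.** Inputs from Sample size analysis: 200 per arm, 72% of controls event-free at one year with the same rate in year two, constant hazard ratio 0.62, and attrition of 7% in each of the first four quarters and 2% in each of the next four. Follow-up is 24 months (Study design). Two-sided alpha 0.05 is assumed; the article does not state it.

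- Quarterly event hazards: control −ln(0.72)/4 = 0.0821; intervention 0.62 × 0.0821 = 0.0509.
- Quarterly attrition hazards: μ₁ = −ln(0.93) = 0.0726; μ₂ = −ln(0.98) = 0.0202.
- Events per arm = 200 × [λ/(λ+μ₁) × (1 − e^(−4(λ+μ₁))) + e^(−4(λ+μ₁)) × λ/(λ+μ₂) × (1 − e^(−4(λ+μ₂)))].
- Control: 200 × (0.531 × 0.461 + 0.539 × 0.803 × 0.336) = 78.0.
- Intervention: 200 × (0.412 × 0.390 + 0.610 × 0.716 × 0.248) = 53.8.
- Total 131.8 events.
- Schoenfeld power: Φ(√131.8/2 × |ln 0.62| − 1.96) = Φ(2.744 − 1.960) = Φ(0.784) = 78.4%, within 2 points of the stated 80%.

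**Step 2: simulate with and without the omitted factors.** Each scenario used 8,000 trials of 400 participants, blocked assignment within strata, the stated attrition, and a control event-free rate held at 72% at one year. Each trial was fitted once with treatment only and once with severity, prior episode and site added. The prognostic hazard ratios are assumed, as are the prevalences (50% high severity, 30% prior episode, 50% per site) and the independence of the three factors.

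*Reading A: 0.62 is conditional on the factors.*

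| Assumed HRs (severity / prior episode / site) | Power, omitted | Power, included | Estimated HR, omitted | Estimated HR, included | Type I error, omitted | Type I error, included |
|---|---|---|---|---|---|---|
| 1 / 1 / 1 | 78.4% | 78.6% | 0.617 | 0.615 | 5.3% | 5.4% |
| 1.5 / 1.5 / 1.2 | 76.0% | 77.7% | 0.624 | 0.617 | 4.6% | 5.3% |
| 2 / 2 / 1.2 | 73.5% | 77.5% | 0.634 | 0.616 | 4.4% | 5.4% |
| 3 / 2.5 / 1.5 | 67.8% | 76.6% | 0.651 | 0.616 | 3.3% | 4.8% |

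The cost of omission is 0.2, 1.7, 4.0 and 8.8 points. The simulation error of a type I rate is about √(0.05 × 0.95/8000) = 0.24 points, so the conservatism is slight in the weak scenario and clear in the strong one.

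*Reading B: 0.62 is the marginal ratio.* The conditional ratio was set to 0.612, 0.600 and 0.582, so that the model without the factors estimates about 0.62 (0.617, 0.615, 0.614).

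| Assumed HRs (severity / prior episode / site) | Power, omitted | Power, included | Gain |
|---|---|---|---|
| 1.5 / 1.5 / 1.2 | 76.8% | 78.4% | 1.6 |
| 2 / 2 / 1.2 | 78.3% | 81.7% | 3.4 |
| 3 / 2.5 / 1.5 | 78.0% | 84.9% | 6.9 |

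**Step 3: size of the shift in the hazard ratio.** The standard error of the log hazard ratio is about 2/√131.8 = 0.174. In the strong scenario the shift is ln(0.651/0.616) = 0.055, about 0.3 standard errors. In the moderate one it is ln(0.634/0.616) = 0.029, under 0.2.

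**The case against.** Several stronger readings are tempting, and the document does not support them.

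- **That the planned hazard ratio is biased towards 1.** The less-adjusted model validly estimates a different, more marginal quantity. It is attenuated only relative to the conditional ratio.
- **That the stated 80% power is wrong.** Sample size analysis uses one control curve, one constant ratio and no covariates. That reads at least as naturally as a marginal ratio, in which case planned power is unaffected and adjustment is an unclaimed gain.
- **That the confidence interval is invalid.** Ignoring the strata errs on the safe side. No excess of false positives follows.
- **That prior episode is a separate omitted stratum chosen because it predicts onset.** Randomization makes it a component of risk severity, and Study design gives the predictive rationale only for the depressed-mood cut-off.
- **That site must be prognostic because coaching differs** ("coaching phone calls either at 1 month (Chicago) or at 2 and 4 weeks and 18 months (Boston"). That difference lies within CATCH-IT, so it bears on a treatment-by-site interaction, which the moderator analysis covers. It does not show that baseline risk differs by site.
- **That provider clustering makes the standard error too small**, since motivational interviews are done "with each provider interviewing one to eight patients". The article gives neither an intraclass correlation nor the number of practices. Health Education participants also have routine contact with their providers, and assignment is blocked by practice. No size can be put on this and it is not part of the point.

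On magnitude, some of the objection stands. Eligibility restricts the CES-D range, and under Phone screen interview those scoring below 8 proceed only with a positive history. That pushes severity and prior episode towards negative correlation, which the simulation ignored, so the strong scenario is towards the upper end. The simulated comparator had treatment only, whereas the planned model has age and sex, which may recover part of the loss.

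What the objection does not remove is the mismatch itself. The interaction test and the moderator analyses do not put severity or site into the main comparison.

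**Conclusion.** The point holds as a matter of efficiency, not of validity. The main Cox model omits risk severity and site, which stratify randomisation. Under the assumed prognostic strengths, the omission costs about 0 to 9 points of power if 0.62 is conditional, with estimated hazard ratios of 0.62 to 0.65. If 0.62 is marginal, it forgoes about 0 to 7 points while planned power stays near 77-78%. Type I error falls to 3.3-4.6% in the prognostic scenarios. The loss is nil if the factors predict nothing, which would sit badly with the article's rationale for the CES-D cut-off.

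The direction is secure. The size is not, because it rests on prognostic strengths, prevalences, independence of the factors and a two-sided 5% level, none of which the article gives. Severity and prior episode probably carry most of the effect; site may add little.

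**What to change.** Prespecify the main Cox model with treatment, baseline CES-D score, prior major depression or dysthymia (yes/no), age and sex, stratified by or adjusted for site. State which CES-D form supplies the covariate, since both the short and the long form appear in the article. State also whether the planning ratio of 0.62 is marginal or conditional. The model with age and sex alone can be reported alongside as the more marginal estimate.

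The cost is small. These factors are already used at randomisation, so no new data are needed. Treatment, CES-D, prior episode, age, sex and site make six parameters, or 131.8/6 ≈ 22 expected events each. In the scenario with no prognostic effect, adding the factors cost no visible power (78.6% against 78.4%). The real trade-off is that the reported hazard ratio becomes conditional on these factors and must be described so. The article reports recruitment still under way (234 of an intended 400 enrolled), so the change could be fixed before any outcome comparison.
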